### Consent

#### School survey

Completion of our school survey did not require consent; completion of the survey assumed schools were happy for the data they were providing to be used. No identifiable information about the school, except the borough which the school is in, will be reported. The school survey and cover letter explained how survey responses will be used.

#### Cross-sectional study

Prior to any data collection for our cross-sectional study, written and informed consent was obtained from schools and parents/guardians, and assent was obtained from children. Schools agreeing to participate were required to complete a consent form signed by the headteacher. At the convenience of the school, a study researcher visited the school to deliver a talk to year three children for 5–10 min about the study. The recruitment packs were given to the children to take home. The recruitment pack included consent and assent forms for parents/guardians and children, respectively. Those who returned completed consent forms (both parent/guardian and their child needed to provide consent and assent) were included for participation in the study. A child who provided assent but their parent/guardian did not was not eligible (and vice versa).

### Data collection: cross-sectional study

There was one time point of data collection per school. Children were visited by a study researcher at their school, who provided the children with an explanation of study involvement and what they needed to do (reiterating the information provided in the information sheet that was included in their recruitment packs) and measured the childrens height and bio-impedance. The children were fitted with the wrist-worn accelerometer on their non-dominant wrist and given a data-collection pack to take home that included instructions of how to wear the accelerometer, duration of wear (7 days a week and worn at all times—not to be taken off during the 7-day wear period), what to do if the accelerometer became uncomfortable to wear and how to contact the study team if the accelerometer was damaged or lost. The recruitment packs also included a paper version of the parent/guardian and child questionnaires (questionnaires were also available to complete online via a link/quick response (QR) code). The front of the pack included the date on which the child should take off the accelerometer and return the accelerometer and completed questionnaires back to the school. The class teachers of participating children were given a questionnaire (paper version) to complete about each participating child’s educational performance. Accelerometers and all questionnaires were collected from the school by the study researcher. Each child who returned their accelerometer and completed questionnaires received a certificate and monetary incentive (Amazon voucher). The study researcher followed up directly with the parent for any accelerometers that were not returned and/or incomplete questionnaires.

### Outcomes and measures

A full description of each WHO’s toolkit six key domains (figure 2)^3^ to promote physical activity during the school day is provided in online supplemental file 1.

**Figure 2 F2:**
[figure not shown]
WHO’s six domains of a whole-school approach to promote physical activity (PA) through schools. Source: WHO, Promoting Physical Activity through Schools: a toolkit. QPE, quality physical education.

#### School survey

Based on the WHO’s six domains of a whole-school physical activity approach (figure 2),^3^ we consulted with teachers to identify schools’ current practices and policies that support a physically active learning environment. We extracted relevant questions from previous studies of children’s physical activity, including SPEEDY,^18^ WAVES^19^ and GoActive,^20 21^ to capture whether schools support the delivery of a whole-school approach. We piloted the survey by asking primary school teachers to provide feedback on flow, response options, language, ease of understanding and the duration of completion. Any changes were reviewed and agreed by the authors and teachers. Two formats of our survey were created, an online version (using Qualtrics software) accessible via a link or QR code and a paper-based version (online supplemental file 2). Based on the responses from the survey, we will derive an ‘Active Environment Score’ for each school.

#### Cross-sectional study

We have collected data on accelerometer-measured physical activity, and through questionnaires, we have collected data on children’s mental health (reported by the parent/guardian) and educational performance (reported by class teachers), detailed in online supplemental file 3. Our outcomes were informed by a core outcome set for assessing school-based physical activity interventions which was jointly produced by the authors and multi-national stakeholders.^22^

#### Physical activity

We used the GENEActiv (ActivInsights Ltd, Kimbolton, Cambridgeshire, UK) wrist-worn accelerometers to measure objective physical activity which has been validated for use among children aged 5–8 years.^23 24^ The GENEActiv is a triaxial STMMicroelectronics accelerometer with a dynamic range of +/-8 g (1 g=9.81 m/s^2^) where *g* represents gravitational unit. It collects raw data on acceleration, is water-resistant (ie, can be worn 24/7) and has been reported to have higher compliance rates than hip-worn accelerometers.^25^ For the HAPPY study, acceleration was sampled at 85.70 Hz to allow for a measurement period of 9 days, capturing a full week (7 days) of data. Data will be extracted using the GENEActiv software and raw data will be processed using 5-second epochs using the GGIR R-package.^26^

#### Mental health

We used the Strengths and Difficulties Questionnaire (SDQ),^27^ a measure of children’s mental health. The SDQ is a brief behavioural screening questionnaire for children and young people aged 2–17 years. It has five subscales which each contain five items that assess emotional symptoms, conduct problems, hyperactivity, peer relationship problems and prosocial behaviour. It has been extensively validated^28^ and is one of the most widely and internationally used measures for assessing children’s mental health.^29^ Scores are derived for each of the subscales, higher scores indicating more difficulties. A ‘total difficulties’ score is calculated by summing the scores for four of the five subscales (excluding the prosocial behaviour subscale).

#### Educational performance

Teachers rated each participating child’s ability for reading, writing and mathematics on a 5-point Likert scale ranging from 1 (below expected levels) to 5 (above expected levels).^30^ Ratings are based on the UK’s National Curriculum’s ‘age-related expectations’ which are the standard expectations defined by threshold descriptors indicating the level pupils should be achieving by the end of primary school.^31^ Teachers also rated the child’s concentration and focus in class using a 5-point Likert scale where scores ranged from 0 (never has difficulties) to 4 (always has difficulties).

### Other measures

We measured anthropometry of all participating children. Height was measured to the last complete mm with a portable stadiometer (Seca, Leicester). A Tanita DC-240 MA Body Composition Analyser (Tanita; Tokyo, Japan) was used to measure weight to the nearest kg and leg-to-leg bioelectrical impedance from which fat-free mass and fat mass will be estimated. Body mass index (BMI) will be calculated as weight (kg)/height squared (m^2^), and fat mass percentage will be calculated as 100× (fat mass in kg/weight in kg).

### Public involvement and engagement

We consulted with primary school teachers to produce our school survey who were involved with the design of questions and approved the final version of the survey. Our questionnaires for the cross-sectional study aimed at parents/guardians and children were based on those used in a previous study which had been piloted.^14^ We are involving teachers, parents and children throughout the duration of our project to ensure that our findings will be translated to schools and relevant community groups.

We have consulted with and will continue to consult with our wider NIHR collaborative groups including our School for Public Health Research Member Collaborators, Advisory Group Members and Practice and Policy Collaborators to increase project impact and produce policy briefings.

### Sample size

The power calculation for this study used a multi-level model to account for the hierarchical structure of the data, with pupils (level 1) nested within schools (level 2). The model included random intercepts to capture variability between schools and examined the relationship between Active Environment Score (maximum score 50 points) and school day physical activity (in min). The analysis adjusted for key covariates such as sex (with females expected to engage in fewer than 10 min of physical activity), ethnicity, weekend physical activity, bioimpedance (used as a proxy for body composition), area deprivation and month of assessment (with higher activity expected during warmer months).

Based on the data collected to date, the sample size analysis included 600 pupils from 20 schools, with an average of 30 pupils recruited per school. The sample size of 600 pupils was the minimum number required for our power calculations; however, we aimed to recruit 1000 children to account for potential data losses (i.e., lost accelerometers, incomplete questionnaires, etc). 17 schools had preobserved Active Environment Scores ranging from 26 to 41, while the scores for the remaining three schools were simulated within this range for consistency.

Power calculations were conducted using Monte Carlo^32^ simulations. We based our effect size on 60 min of physical activity per day (recommended global guidelines), of which 30 min should take place during the school day. We hypothesised that schools’ Active Environment Score would contribute to changes in the baseline; thus, an effect size of 0.50 would be clinically significant. However, we also explored a range of effect sizes, from 0.30 min to 1.00 min per unit increase in the Active Environment Score. The results indicated that the study achieves 81% power when a unit increase in the Active Environment Score corresponds to a 0.55-minute increase in physical activity. For increases of 0.70 min or more per unit of the Active Environment Score, the study achieves over 90% power, demonstrating a strong capability to detect these changes (see figure 3). These findings indicate that the study is well-powered to detect meaningful differences in physical activity when the Active Environment Score has a measurable impact, particularly for changes of 0.55 min or more per score unit. This provides confidence that the study design is adequate for identifying associations of this magnitude under the current assumptions.

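### The power claim is tied to a slope of 0.55 min per score unit, but the slope called clinically significant is 0.50, where the 20-school design has about 73% power

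*Protocol article*

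**What the plan says.** All the statements are in the Sample size section of the protocol article.

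- **Target effect.** After recalling the 60-minute daily guideline and its 30-minute school-day share, the text says "thus, an effect size of 0.50 would be clinically significant". No unit is attached, but the next sentence supplies one: "we also explored a range of effect sizes, from 0.30 min to 1.00 min per unit increase in the Active Environment Score".
- **Design simulated.** "the sample size analysis included 600 pupils from 20 schools, with an average of 30 pupils recruited per school". The scores ran from 26 to 41; 17 were observed and three simulated.
- **Power reported in the text.** There are two points on the curve: "the study achieves 81% power when a unit increase in the Active Environment Score corresponds to a 0.55-minute increase in physical activity", and "For increases of 0.70 min or more per unit of the Active Environment Score, the study achieves over 90% power".
- **Conclusions.** The text says that "the study is well-powered to detect meaningful differences in physical activity", adding that this applies particularly from 0.55 min per unit upward. It also says "The sample size of 600 pupils was the minimum number required for our power calculations", and explains the larger aim by attrition: "we aimed to recruit 1000 children to account for potential data losses".

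The text gives no power at 0.50, no target power, and no significance level or number of runs for the simulation. Figure 3 plots power against effect size but is not visible in the copy reviewed.

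**The concern.** The section gives a clinical reason for one slope and a power figure for another. A reader who sees 0.50 named as clinically significant, then 81% power, then a claim of good power for meaningful differences, will take 81% as the power for the meaningful difference. It belongs to a slope 10% larger: across the 15-point score range, 8.25 min (15 × 0.55) rather than 7.5 min (15 × 0.50). Power rises with the slope, so power at 0.50 must be lower.

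This is the article's only power justification for the main outcome. If the primary association turns out null, readers will use this section to judge how far a meaningful association has been ruled out. For the design simulated, they would put the chance of missing the target slope at 19% (100 − 81), when the article's own figures imply about 27% (100 − 73).

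**Working it through.** **Can the 81% be reproduced?** Not from first principles. The pupil-level SD, the intraclass correlation (ICC) or between-school variance, the SD of the score, the covariate effects, the significance level and the number of runs are not given. The check therefore calibrates on the article's own point and moves along the same power curve, which needs no SD or ICC.

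**Inputs.** Power 0.81 at slope 0.55; more than 0.90 at 0.70; 600 pupils in 20 schools (all from Sample size). The two-sided 5% level is an assumption, suggested by the 95% CI in Statistical analysis.

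**Step 1: implied standard error of the slope.**
SE = 0.55 / (z₀.₉₇₅ + z₀.₈₁) = 0.55 / (1.960 + 0.878) = 0.194 min per unit.

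**Step 2: consistency with the second published point.**
Power(0.70) = Φ(0.70/0.1938 − 1.960) = Φ(1.65) = 95%. This agrees with the stated figure of over 90%.

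**Step 3: power at the target slope.**
Power(0.50) = Φ(0.50/0.1938 − 1.960) = Φ(0.62) = 73%.

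**Step 4: the reverse check.** A design with 80% power at 0.50 has 0.50/SE = 1.960 + 0.842 = 2.802. At 0.55 the ratio is 1.1 × 2.802 = 3.082, so power is Φ(3.082 − 1.960) = 87%. The article reports 81%.

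**Step 5: sensitivity of the 73%.**

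| Variant | Power at 0.50 |
|---|---|
| Two-sided 5%, normal reference | 73.2% |
| 81% read as 80.5% to 81.5% (rounding) | 72.7–73.8% |
| t reference, 10 to 18 df, two-sided | 73.3% |
| One-sided 5% | 74.2% |
| Simulation error, 1000 runs | 71–76% |
| Simulation error, 500 runs | 70–77% |
| Simulation error, 200 runs | 67–79% |
| Simulation error, 100 runs | 65–82% |

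The simulation-error rows take 0.81 ± 1.96·√(0.81 × 0.19/R) and pass each limit through Steps 1 and 3. Only at about 100 runs does the range include 80%.

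**Step 6: the design actually targeted.** Study setting and population gives a target of up to 1000 children from about 40 schools. With k schools of m pupils, the variance of the slope is proportional to [ICC + (1 − ICC)/m]/k, assuming the same spread of scores. For an assumed ICC of 0.05:

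- 20 schools of 30: (0.05 + 0.95/30)/20 = 0.00408
- 40 schools of 25: (0.05 + 0.95/25)/40 = 0.00220
- Ratio of standard errors = √(0.00408/0.00220) = 1.36
- Power(0.50) = Φ(2.58 × 1.36 − 1.96) = 94%

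Over assumed ICCs of 0.02 to 0.15, power at 0.50 is 93–95% for 40 schools of 25 (1000 analysable) and 82–92% for 40 schools of 15 (600 analysable).

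**The case against.** Several points on the other side have force.

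- **Figure 3 may show the value at 0.50.** The explored range covers it. A reader might infer that the plan never reports power at its target; this copy cannot establish that. Only the text can be said to omit it, and the text still draws the conclusion at issue.
- **No target power is stated.** That stands. The 80% benchmark is inferred from the prominence of the 81% point. Even without it, the power figure and the clinical justification belong to different slopes.
- **The 73% rests on one simulated point.** This also stands. The Figure 3 legend acknowledges irregularities from simulation noise, and the fitted curve reaches 90% at about 0.63 (0.1938 × (1.960 + 1.282) = 0.628), whereas the text claims it only from 0.70. That does not help the 0.50 case, but it means the 73% is approximate. The study team holds the exact simulated value.
- **The conclusion is partly hedged.** It singles out 0.55 and above, and the closing sentence of that paragraph limits adequacy to associations of that size. However, singling out is not limiting: the claim still covers meaningful differences, and 0.50 is the value the section names as such.
- **More schools were targeted.** A reader might infer that the completed study has a 27% chance of missing the target slope. The documents do not support that. The 27% belongs to 600 pupils in 20 schools, the target was about 40 schools, and the final number is not reported.

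**Conclusion.** The inconsistency is real and lies in the text. For 600 pupils in 20 schools, power at the slope called clinically significant is about 73%, against the 81% reported at 0.55. The claim of good power for meaningful differences, and the description of 600 pupils as the minimum required, do not hold at 0.50 for that design.

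This rests on reading 0.50 as minutes per score unit, on a two-sided 5% test, on 80% as the implied benchmark, and on a simulation with more than about 100 runs.

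It does not show that the completed study is underpowered: with about 40 schools, power at 0.50 could exceed 80% or even 90% under the assumed ICCs. Nor does it justify putting a new required number of schools into the plan. Data collection has ended, so that would rewrite a planning statement after the fact. What needs correcting is a reported justification; no recruitment or analysis step is affected.

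**What to change.** In Sample size:

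1. State the simulated power at 0.50 min per unit for 600 pupils in 20 schools, taken from the existing simulation (expected to be about 73%), with the number of runs and the significance level.
2. Limit the well-powered claim to slopes of about 0.55 and above, or justify 0.55 as the target difference in place of 0.50.
3. Qualify the description of 600 pupils as the minimum, so that it refers to a slope of 0.55.
4. Rerun the simulation at 0.50 with the final number of schools and analysable pupils, and report that figure beside the 20-school one.

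The cost is a few sentences and one rerun of existing code, before the analysis starts. No further recruitment is needed. The figure for the 20-school design will look less favourable; the figure for the final sample may look better.

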**Figure 3 F3:**
[figure not shown]
Power versus effect size for the Health and Activity of Pupils in the Primary Years study.

The statistical power of the multi-level model, based on 600 pupils nested within 20 schools, is shown across a range of effect sizes (minutes of physical activity per unit increase in the Active Environment Score). While power generally increases with larger effect sizes, the minor irregularities observed in the power curve can be attributed to the stochasticity inherent in Monte Carlo simulations, where random variability in the data leads to slight fluctuations in the results.

### Statistical analysis

All data collection for the study has been completed. The data are being processed and cleaned in preparation for the analysis. We will characterise features of our study population including child sex, ethnicity and adiposity. We will report characteristics of schools including school size, ethnic mix, Ofsted rating, percentage eligible for free school meals and area-based deprivation. We will present school and pupil level baseline characteristics by active environment scores with summary measures (totals, percentages, means and SD, medians and IQRs as appropriate).

The main analysis will treat the main outcome (physical activity during the school day) as a continuous variable. Decisions on valid accelerometer data to include in the analysis will be made when reviewing the data. We will use mixed-effects regression models to estimate the association between physical activity acceleration and the active school environment score. We will include pupil-level covariates (sex, ethnicity) and account for clustering at the school level by including random effects. Covariates will be included in the model in stages to assess how much each contributes to diluting or increasing the effect. To measure equity, the primary analysis will adjust for pre-specified school characteristics including school size, pupils eligible for free school meals, pupils whose first language is not English, children with Special Educational Needs and Disabilities and area-level deprivation. Sensitivity analysis will include clustering at the class-level within the school.

Results will be reported with a 95% CI. Mixed effects regression models as described for physical activity will be repeated for the outcomes of mental health and educational performance. All analyses will be carried out using Stata v18.5 and R statistical software. We will report our findings in line with the Strengthening the Reporting of Observational Studies in Epidemiology^33^ and Logical Explanations & Visualizations of Estimates in Linear mixed models guidelines^34^ for reporting cross-sectional studies.

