### Study setting and population

Our school survey was distributed to all state-funded primary schools in Greater London (n=1826). For our cross-sectional study, primary schools were recruited to participate, through which we invited children in year three (aged 7–8 years; one of the age groups identified as the least active in the primary school years^12^) and their parent/guardian to participate. All children in year three were eligible for participation, but participation was optional. Completion of both consent (adult) and assent (child) was required to participate in the study. Our target, based on our previous work,^14^ was to recruit up to 1000 children from approximately 40 schools across Greater London.

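### Step changes from staged covariate entry will be read as each covariate's own contribution, but they depend on entry order and, with few schools, on chance

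*Protocol article*

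**What the plan says.** The Statistical analysis section sets out a mixed-effects regression of physical activity on the Active Environment Score. On pupil covariates and clustering it says "We will include pupil-level covariates (sex, ethnicity) and account for clustering at the school level by including random effects". It then states both a procedure and the inference to be drawn from it: "Covariates will be included in the model in stages to assess how much each contributes to diluting or increasing the effect".

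On school characteristics it says that "the primary analysis will adjust for pre-specified school characteristics", and the list includes "school size, pupils eligible for free school meals, pupils whose first language is not English, children with Special Educational Needs and Disabilities", followed by area-level deprivation. That is at least five school-level covariates. The aim given for this adjustment is to measure equity. The same models are to be repeated for mental health and educational performance.

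On numbers of schools, the Sample size section says "the sample size analysis included 600 pupils from 20 schools, with an average of 30 pupils recruited per school", while Study setting and population gives a target to "recruit up to 1000 children from approximately 40 schools across Greater London". The number finally recruited is not stated.

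**The concern.** When a covariate enters a model, the score coefficient changes by an amount that depends on what is already there. If two school characteristics carry much the same information, whichever enters first absorbs most of their joint effect and the second appears to add little. Free school meals eligibility and area-level deprivation are both markers of disadvantage and plausibly overlap in this way.

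There is a second, separate difficulty. The school covariates vary only between schools, so the school is the unit that counts for them. With a few dozen schools at most, even an irrelevant covariate is correlated with the score by accident and moves its coefficient. Read as the plan proposes, that movement would be called dilution or strengthening.

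What is at stake is any statement about how much a particular characteristic accounts for the association. Equity is one of the study's three research questions and policy briefings are a planned output, so such statements could be given weight.

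**Working it through.** **The plan's own figure.** The Sample size section reports 81% power at 0.55 min per score unit with 600 pupils in 20 schools. The outcome SD, intraclass correlation and alpha are not given, so this cannot be rebuilt from scratch. It does imply a standard error. With two-sided 0.05 assumed, SE = 0.55 / (1.960 + 0.878) = 0.194. Power at 0.70 is then Φ(0.70/0.194 − 1.960) = 95%, which agrees with the stated figure of over 90%. The power figures are not in dispute; the SE serves only to set a realistic noise level below.

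**1. Order dependence**

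Take the score and two covariates, all standardised. Let the covariates have equal effects γ, correlation r with each other and correlation q with the score. Let β be the fully adjusted score coefficient.

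- Crude coefficient: β + 2γq
- With one covariate in: β + γq(1 − r)/(1 − q²)
- With both in: β

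The total change is 2γq, so the shares are:

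- entered second: (1 − r) / [2(1 − q²)]
- entered first: 1 minus that

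γ cancels. Example with r = 0.5 and q = −0.3: 0.5 / (2 × 0.91) = 0.275, so 27% second and 73% first.

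| r (assumed) | first / second, q = −0.3 | first / second, q = −0.5 |
|---|---|---|
| 0.2 | 56% / 44% | 47% / 53% |
| 0.5 | 73% / 27% | 67% / 33% |
| 0.7 | 84% / 16% | 80% / 20% |
| 0.9 | 95% / 5% | 93% / 7% |

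With five equally correlated covariates and q = −0.3, a covariate's share entered first versus last is 38% vs 9% at r = 0.3, 56% vs 5% at 0.5, 74% vs 2% at 0.7 and 91% vs 1% at 0.9. At r = 0 the pattern reverses (12% vs 31%).

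In minutes, assume a score SD of 4.6, covariate effects of −1.5 min per SD, and two covariates reflecting one latent factor that correlates −0.4 with the score. A covariate's mean step change in the slope, first versus second, is then about −0.07 vs −0.05 at r = 0.2, −0.14 vs −0.05 at 0.5, −0.18 vs −0.04 at 0.7 and −0.23 vs −0.01 at 0.9. These means are almost the same at 20 and 40 schools.

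**2. Chance movement**

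Inputs: the score SD is 4.6, the SD of whole-number scores spread evenly over 26 to 41, the range in the Sample size section ("17 schools had preobserved Active Environment Scores ranging from 26 to 41"). The residual SD of a school mean is set at 3.9, which gives 3.9 / (4.6 × √20) = 0.190, close to the implied 0.194. The true slope is 0.50.

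Adding k irrelevant school covariates with J schools shifts the slope with

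variance = [3.9² / (4.6² × (J − 3))] × k / (J − 3 − k).

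- J = 20, k = 1: 0.0423 × 1/16, SD 0.051
- J = 20, k = 5: 0.0423 × 5/12, SD 0.133
- J = 40, k = 1: 0.0194 × 1/36, SD 0.023
- J = 40, k = 5: 0.0194 × 5/32, SD 0.055

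Simulation gives the same SDs to within 0.001. The probability of a shift larger than 0.05 (10% of 0.50) is about 20% for one covariate and 62–63% for five at 20 schools, and about 5% and 30–31% at 40 schools.

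**The case against.** Several counter-arguments have force.

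- **The main estimate is safe.** The fully adjusted score coefficient is the same whatever order the covariates enter. This stands, and it confines the point to a secondary reading.
- **The size rests on assumed correlations.** A reader might infer that nearly the whole change would go to whichever covariate enters first. The documents do not support that: it needs a correlation near 0.9, and no correlations are given. At 0.2 there is little or no advantage to entering first. School size, language and special educational needs need not track free school meals closely.
- **Twenty schools is not the cause.** A reader might also blame the order effect on there being only about 20 schools. Overlap produces it: in simulation the median shares were almost the same with 20, 40 and 400 schools. Few schools only make the split less stable. Moreover, 20 is the power-calculation figure and the target was approximately 40, at which the chance shifts more than halve.
- **Sign disagreement is weaker than it looks.** In simulation with 20 schools, the sign of a covariate's step change differed by order in 21%, 28% and 41% of datasets at correlations 0.5, 0.7 and 0.9. Much of this is noise around a second-step change close to zero.
- **The 10% cut is not the plan's.** True; the plan sets no threshold. The cut is only a yardstick for visible movement.
- **Order and composition of stages may be in an analysis plan.** They may, and their absence from an article is no fault. But a fixed order would only make the step changes reproducible. They would still be conditional contributions, which is not what the sentence says they show.

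**Conclusion.** The point holds as a fault in a stated interpretation. Staged entry does not measure each covariate's contribution when covariates overlap. With two covariates correlated at 0.5 to 0.9, the same one receives 67–95% of the change if first and 5–33% if second. This assumes equal effects and score correlations of −0.3 or −0.5. At low correlation the gap is small, and the true correlations are unknown.

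Chance movement is a separate and additional problem. Five irrelevant school covariates move the slope by more than 0.05 in about 62% of datasets at 20 schools and 30% at 40, given a school-mean residual SD of 3.9 and a score SD of 4.6. The general promise of 95% intervals for results is not tied to these step changes.

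The adjusted association itself is not in question, and the plan should not be read as yielding a biased primary estimate on this account.

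**What to change.** Replace the sentence on staged entry with three fixed blocks: crude; plus pupil covariates; plus all pre-specified school characteristics together. Report the crude and fully adjusted score coefficients, and interpret only the change from block to block, with an interval from a bootstrap that resamples schools. Blocks alone do not remove chance movement, because the school block carries all five covariates; the interval is what shows it.

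For single covariates, either delete the clause about each one's contribution, or take contributions from the full model with an order-invariant decomposition (Gelbach) and its interval. Dropping one covariate at a time is not a substitute: it returns the entered-last quantity, so two overlapping covariates could both appear negligible despite a sizeable joint effect.

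The cost is one sentence and a few lines of code. According to the article the data are still being processed and cleaned, so the change can be made before analysis. The downside is fewer statements about individual covariates, with wider intervals.
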